### Randomization

After completion of the baseline visit, all participants will be randomized according to a pre-defined protocol. For this purpose, the project statistician will implement an independent, web-based procedure for random group allocation using a randomization tool provided by the Research Electronic Data Capture Software (REDCap) [72]. After randomization by designated study personnel, the patient, the study center, and the trial management team will be informed about the respective allocation.

### Blinding

Due to the nature of the intervention, all participants and staff members in the prehabilitation centers cannot be blinded. Therefore, blinding to group allocation will be limited to outcome assessors. The project coordinator, data manager, and the intervention coordinator will have access to group assignment but will not be involved in assessing participants in the follow-up phase (baseline visit assessments will be conducted prior to randomization).

### Data collection and follow-up

#### Documentation

With the exception of V4 and V5, data from all visits will be recorded directly into the REDCap system. Access to the database is controlled by a password and is granted through the management committee.

The data structure of the database has been designed to ensure a comprehensive and consistent data entry, with controls for range and adequacy, and automated score calculation to minimize errors. Whenever possible, pre-selected options were provided to replace free data texts.

Data quality will be ensured by (a) regular validation of the data by the study team, including checks for comprehensibility, and (b) by re-education visits for all recruitment and prehabilitation centers, if necessary.

Personal information of participants will only be collected after a signed consent form is available. Personal data will include the name, residency, and contact data of all participants. Additional information will include contact data of relatives or significant others, primary care physicians, and care institutions. Due to data safety reasons, this sensitive data will be recorded in a separate REDCap database with a three-factor authentication procedure.

All therapy sessions within the prehabilitation program can be documented directly in REDCap, with a paper-based backup option. Documentation for each session includes goals, performed exercises, duration of the session, intensity, number of sets, and equipment used (e.g., weights). The prescription of unsupervised exercises will be documented additionally. The therapist responsible for each session will provide the documentation.

After completing the study, all gathered data will be stored within the secured data storage system of the leading study center (Charité – Universitätsmedizin Berlin).

#### Patient diary

Each patient will be asked to keep a prehabilitation diary for the documentation of the unsupervised sessions. The diary includes the same items as the form used by the therapists. Completion of the diary will be controlled during the supervised sessions by the therapist working with the patient.

#### Follow-up visits

All participants will be contacted for follow-ups monthly for 12 months after surgery (see Table 2). Telephone interviews (visits 7, 8, and 10 to 17) will cover the incidence of falls within the previous month, the current medication, current pain, and the use of medical, nursing, or therapeutic services. In addition to those items, visits 9, 12, and 15 will assess the quality of life (EQ-5D-5L), disability (WHODAS 2.0), and questions regarding the use of healthcare resources (FIMA).

Three months after surgery, the telephone interview (V9, see Table 2) may be extended to a home or study center visit. In this case, the same assessment as in the final follow-up (V18) will be performed, including all functional performance tests. If the visit cannot be arranged, a shortened test battery will assess all information that can be obtained by telephone.

Visit 18 takes place as a home or study center visit for all included study participants. During this visit, a final assessment of the nursing care dependency level is carried out by means of the NBA, as well as all other assessments initially recorded in visits 0 and 2, so as to identify different trajectories within the two study groups.

Retention of the enrolled participants will be promoted by the monthly telephone interviews, which will serve not only to gather data, but also to allow study personnel to “stay in touch” with the participants.

### Sample size and power considerations

Based on the current literature [73], Table 4 shows the assumed changes in the level of care dependency in the intervention and control groups.

**Table 4 Tab4:** Quantification of the intervention effect according to Müller-Mai et al

Change in care level	Intervention group	Control group
Improvement of ≥ 1 level	5%	2.5%
No change	47.5%	42.5%
Reduction of 1 level	45%	50%
Reduction of ≥ 2 levels	2.5%	5%
Sum	100%	100%

Formally, the probability of changes in the level of care is an ordered categorical outcome, so the sample size was calculated according to Kolassa [74], using the nQueryAdvisor V7 (MTT2-tmpB3E4 modules; Statsols, Cork, Ireland). Based on this calculation, a sample size of 470 patients in each group will have 80% power to detect the expected quantified effects shown in Table 4, using a Wilcoxon-Mann-Whitney rank sum test with a 0.05 two-sided level. Considering a 2.5% rate of incorrect treatment allocation and 30% loss to follow-up after 12 months, the targeted sample size of the trial is *n* = 1378.

The initial recruitment plan wanted to achieve 1378 participants within a 12-month period. Due to the COVID-19 crisis, the recruitment phase was extended by additional 12 months to a total of 24 months.

### Discontinuing or modifying the allocated intervention (prehabilitation)

All deviations from the intervention protocol will be documented. Possible deviations include, but are not limited to, deviations from the duration of the intervention, as well as changes in the defined goals or setting due to medical or organizational issues, inadequate patient compliance, or drop-out of the study.

### Documentation and reporting of adverse and serious adverse events

Adverse events may occur spontaneously and are expected within our study population, so non-serious adverse events (AEs) (defined as any non-critical and “untoward medical occurrence in a patient or clinical investigation subject administered an investigational intervention”) do not necessarily have a causal relationship to the intervention (adapted from the Note for Guidance on Clinical Safety Data Management: Definitions and Standards for Expedited Reporting (CPMP/ICH/377/95 July 2000)). According to the judgment of the investigator, AEs will be documented as part of the study CRF if an event is considered to be of concern or related to the study or the intervention. Adverse events will be collected from the time of enrollment in the trial until 48 h after the final assessment. Developments will be documented until the event is resolved or explained (max. until day 379 (365 + 14) after elective surgery). The frequency of follow-up is left to the discretion of the investigator.

Serious adverse events (SAEs) are defined as unexpected, fatal, or life-threatening events that are potentially related to the study intervention. An investigator must report the event in the eCRF within 72 h of the first notification. Serious adverse events will be reported up to 48 h after the last study visit, including the following:Events occurring during prehabilitation sessions: falls, cardiac arrest, unscheduled hospitalization, unscheduled intervention (e.g., cardiac catheter), or unscheduled surgeryEvents occurring during study visits in the hospital or at home (from the start of the visit up to 48 h after the visit): falls

Insurance is provided to all participants for any adverse event related to study visits or the intervention (including traveling to and from the study/prehabilitation site).

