### Interventions

The control group will receive no intervention aside from the usual care provided as part of the surgery process and subsequent rehabilitation. The “usual care” comparator appears to be the appropriate option for a pragmatic effectiveness analysis.

The intervention group will receive (1) a shared decision-making (SDM) conference and (2) a 3-week individualized prehabilitation program prior to the elective surgery. Study participation will have no influence on intra- and postoperative processes, such as the scope rehabilitation programs.

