### Management committee and data safety monitoring committee

A management committee (MC) and a data safety monitoring committee (DSMC) have been established to ensure transparent and safe study practices.

The MC is responsible for developing the study protocol, training of all assessors and healthcare professionals involved in the intervention, and for the initiation of new study centers. Additionally, the MC will monitor the study procedures in all study centers and will ensure adherence to measurement and intervention protocols, as well as ethical guidelines. Deviations from any protocol will be documented and reported.

An independent data and safety monitoring committee (DSMC), consisting of experts in clinical studies, biostatistics, and perioperative and rehabilitation medicine, has been established to monitor recruitment, protocol adherence, and monitoring of follow-up and safety data. Virtual and face-to-face meetings will be regularly conducted, whereas both committees may independently request video conferences. The results of all meetings will be documented in protocols. The DSMC will assess the trial progress and safety, and accumulated trial data will be reported to the DSMC by the study statistician. As a primary responsibility, the DSMC will consider and assess treatment safety (e.g., serious adverse events (SAEs) or deaths). If necessary, recommendations will be made by the DSMC to the MC regarding stopping or continuing the trial. At their discretion, the DSMC may also formulate recommendations relating to the selection/recruitment of participants, their management, improving adherence to protocol-specified regimens and matter relating to patient retention, and procedures for data management and quality control.

The MC will be responsible for promptly assessing any DSMC correspondence or recommendations, to decide whether to continue or terminate the trial, suspend enrolment, or determine whether amendments to the protocol or changes in study conduct are required.

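### SAEs are defined by relatedness to the intervention and listed mainly for prehabilitation sessions, so SAE counts cannot be compared between arms and unrelated serious events lack a clear reporting route

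*Protocol article*

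**What the plan says.** All references are to the protocol article. The section on documentation and reporting of adverse and serious adverse events states that SAEs "are defined as unexpected, fatal, or life-threatening events that are potentially related to the study intervention". It continues: "Serious adverse events will be reported up to 48 h after the last study visit, including the following". Two items follow. The first begins "Events occurring during prehabilitation sessions: falls, cardiac arrest, unscheduled hospitalization" and goes on to unscheduled interventions and unscheduled surgery. The second covers falls only, from the start of a study visit in hospital or at home to 48 h after it.

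The same section describes adverse events (AEs) as non-serious and non-critical. They are recorded, at the investigator's judgement, "if an event is considered to be of concern or related to the study or the intervention". On timing it says: "Adverse events will be collected from the time of enrollment in the trial until 48 h after the final assessment".

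Under Interventions: "The control group will receive no intervention aside from the usual care provided as part of the surgery process and subsequent rehabilitation". Table 2 marks both the shared decision-making phase and the prehabilitation phase as intervention group only. On oversight, "the DSMC will consider and assess treatment safety (e.g., serious adverse events (SAEs) or deaths". The committee also receives accumulated trial data from the study statistician.

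**The concern.** An SAE count is useful for comparing harm only if the same event in either arm has the same chance of being counted. Here whether an event counts depends on a judgement about a treatment that one arm does not get, and on a list built mostly around sessions that one arm does not attend. A difference in SAE counts would then mix any real difference in harm with a difference in the counting rule.

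The second problem is a gap in the categories. AEs are non-serious, and SAEs must be potentially related. A serious event that nobody attributes to the intervention fits neither. In frail or pre-frail patients aged 70 or over, such events are to be expected. The period before surgery also matters for this intervention, because prehabilitation occupies about three weeks of it. If harm arises through events that look unrelated, the SAE channel is not designed to show it.

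**Working it through.** The safety section gives no event rate and no safety power, so there is no figure to reproduce. The check sets the rules side by side.

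**1. The list by arm.** Session events: fall, cardiac arrest, unscheduled hospitalisation, unscheduled intervention, unscheduled surgery (5). Visit events: fall (1). Sessions exist only in the intervention arm, so 5 of 6 combinations cannot occur in a control.

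**2. The rules applied to example events.**

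| Event | SAE by definition? | On the list? | AE? | Other record |
|---|---|---|---|---|
| Cardiac arrest in a session | If potentially related | Yes | No, serious | Hospital or emergency record |
| Cardiac arrest at home between sessions, intervention arm | Only if potentially related | No | No, serious | Hospital or emergency record |
| The same event in a control before surgery | Hardly possible | No | No, serious | Hospital or emergency record, if it is found |
| Unplanned admission of a control, months after surgery | Hardly possible | No | No, if serious | Resource-use questionnaire |
| Fall within 48 h of a study visit, either arm | Depends on reading | Yes | Depends on reading | Falls monitoring |
| Death, either arm | Only if potentially related | No | No | Mortality documentation |

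The second and third rows are the same clinical event under different rules. The third has no clear safety-reporting category.

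**3. What this does to a comparison.** Let r be the true risk of a serious event, equal in both arms, and f the share judged potentially related. Leaving aside falls around visits, the SAE risk is r × f(intervention) against r × f(control). With f(control) close to 0, the difference is about r × f(intervention). This is not zero although the true difference is zero. The article gives neither r nor f, so no number can be attached.

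**4. Coverage over time.** In Table 2, controls have no scheduled contact between the baseline visit (V2) and discharge (V6), while the intervention group has V3 to V5. Monthly contacts, and resource use as an outcome, are timed from surgery. A participant who deteriorates and never has surgery has no date from which V6 to V18 can be counted. Falls are the exception: they are monitored over the whole study and asked about since the last visit.

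**5. The wording of the definition.** The three adjectives can be read in two ways. If *unexpected* is required in addition to fatal or life-threatening, a session fall without threat to life fails the definition but is on the list. If *unexpected* is an alternative, an unexpected session fall qualifies, but so does any unexpected related event, however minor. The article does not say which is meant.

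**The case against.** The strongest reply is that harm data exist outside the SAE channel. The assessments section documents mortality, emergency visits, planned and unplanned hospital stays, and peri- and postoperative complications, with no relatedness test and no restriction by arm. Falls are monitored throughout. The DSMC receives accumulated trial data, SAEs and deaths are only examples in its remit, and regular safety reports are sent to it. This stands. A reader might infer that the committee cannot compare harm between arms at all; the article does not support that.

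The list is introduced as inclusive. A life-threatening event at home that is potentially related is an SAE whether listed or not. Thirty sessions of 30 minutes make 15 h out of 21 × 24 = 504 h, or 3.0%, and a reader might conclude that the other 97% of the prehabilitation period is unreportable. That figure describes only what the session item covers, not what is reportable.

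A reader might also expect high SAE counts in the intervention arm. Without an event rate this is unsupported; the counts are unequal in construction, but their level is unknown. Nor does the article say that relatedness is always judged by unblinded staff. Centres are told the allocation and outcome assessors are blinded, but who makes the judgement is not specified.

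AEs can be recorded when merely of concern, without relatedness, from enrolment and in either arm. That helps for non-serious events. It does not clearly help for serious ones, which the AE description excludes.

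Finally, this is a condensed article. The full protocol may be clearer, and table layouts for the committee commonly sit in a charter, so their absence is no fault. The definition and the list, however, are stated here and can be judged as stated.

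**Conclusion.** The point holds in a limited form. SAE counts as defined are structurally unequal between arms (5 of 6 listed combinations are closed to controls, and relatedness is part of the definition) and should not be read as a between-arm comparison of harm. Serious events not judged related have no clear reporting category, and this gap is widest between randomisation and surgery. Of the two safety measures named for the DSMC, deaths are comparable and SAEs are not. Other outcomes documented in both arms remain available to it.

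This rests on reading the definition as written, on investigators seldom relating a control's event to an intervention the patient did not receive, and on the full protocol not saying otherwise. The consequence cannot be expressed in events from the article. It is a weakness in safety monitoring and does not touch the primary efficacy analysis.

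**What to change.** Amend the safety section as follows.

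- Define an SAE by seriousness criteria alone, regardless of cause, and collect SAEs in the same way in both arms from randomisation.
- Record relatedness and expectedness as separate fields, and name who judges them.
- Reconcile the definition with the event list, and state whether *unexpected* is a required condition or an alternative.
- Base the DSMC's between-arm comparison on tables by arm of all deaths, unplanned admissions and emergency visits, counted from randomisation, with participants who never reach surgery included.
- Keep the session events as an additional listing for the intervention arm, not as a comparison.

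If the full protocol already separates seriousness from cause, it is enough to align the article with it. Otherwise the cost is a safety-section amendment and more event entries. Most of the data for the tables are already collected; the main addition is asking about the interval between randomisation and surgery in both arms.

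### SAE counts follow a different entry rule in each arm, because an SAE must be potentially related to an intervention that controls do not receive; they cannot support a between-arm safety comparison

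*Protocol article*

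**What the plan says.** All of the following is in the Protocol article.

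- **SAE definition** (Documentation and reporting of adverse and serious adverse events): SAEs are those unexpected, life-threatening or fatal "events that are potentially related to the study intervention". Two groups are then listed. The first begins "Events occurring during prehabilitation sessions: falls, cardiac arrest, unscheduled hospitalization" and goes on to unplanned interventions and surgery. The second covers only falls at a hospital or home study visit, up to 48 h after it.
- **Non-serious events** (same section): "According to the judgment of the investigator, AEs will be documented" in the CRF "if an event is considered to be of concern or related to the study or the intervention". The window is not limited to one arm: "Adverse events will be collected from the time of enrollment in the trial until 48 h after the final assessment".
- **Control arm** (Interventions): "The control group will receive no intervention aside from the usual care provided as part of the surgery process" and later rehabilitation.
- **Who knows the allocation** (Randomization; Blinding): the patient, the centre and trial management are told; only outcome assessors are blinded.
- **Use of the data** (Management committee and data safety monitoring committee): "As a primary responsibility, the DSMC will consider and assess treatment safety (e.g., serious adverse events (SAEs) or deaths").

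**The concern.** Relatedness is normally an attribute recorded for each event. Here it is part of what makes an event an SAE, and it refers to something only one arm receives. A table of SAEs by arm would then reflect the entry rule as well as the patients' experience.

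What is at stake is the DSMC's reading of safety. A strategy that places a 3-week programme before surgery could do harm through ordinary events that no investigator would call related in a single patient. Such harm shows only as an excess over control. Conversely, closer observation of one arm can produce an excess where none exists.

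**Working it through.** The article gives no adverse event or SAE rate, so there is no figure of its own to reproduce on this point. The check is mainly a comparison of rules.

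**1. Routes to an SAE, by arm**

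| Route | Intervention | Control |
|---|---|---|
| General definition (potentially related to the intervention) | can be met | can hardly be met: no intervention received |
| Listed: falls, cardiac arrest, unplanned admission or procedure during a session | open | closed: no sessions |
| Listed: fall at a study visit or within 48 h | open | open |

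Take the same life-threatening event before surgery in two patients. In the intervention arm it is an SAE if judged possibly related. In the control arm it has practically no route in.

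**2. What the counts can identify**

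Expected recorded events in an arm = n × r × c, where r is the true risk and c the share of events that the rule admits and staff notice. With equal n, the ratio of counts is (r_I / r_C) × (c_I / c_C). It equals the risk ratio only if c_I = c_C. For SAEs other than falls around visits, the rule pushes c_C towards 0, while c_I is unknown.

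**3. Contact before surgery** (Prehabilitation; Table 2)

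- Intervention: 10 supervised sessions a week × 3 weeks = 30 sessions, on 5 × 3 = 15 days, besides V3 to V5.
- Control: V3 to V5 do not apply, so no visit is planned between V2 (baseline and randomisation) and V6 (7–14 days after surgery).

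The looser rule for non-serious events therefore also works on unequal observation in this interval.

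**4. What is recorded without the filter, and when**

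- Deaths, and emergency visits from hospital, insurer or discharge-letter sources (Assessments): not confined to the time after surgery.
- Falls since the last visit, asked at each visit after baseline (Assessments): at V6 this reaches back to V2 in controls.
- Peri- and postoperative complications (Outcome measures).
- Planned and unplanned hospital stays through FIMA (Assessments): resource use is defined for the 12 months after surgery (Outcome measures), and the monthly contacts start after surgery (Follow-up visits).

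The interval from randomisation to surgery is thus only partly covered.

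**5. Illustration, on assumed risks only**

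n = 1378 / 2 = 689 per arm (target in Sample size and power considerations, 1:1 allocation). All risks and recorded shares below are assumptions.

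*False excess.* True risk 10% in both arms, 80% against 40% recorded:
- Counts: 689 × 0.10 × 0.80 = 55.1 and 689 × 0.10 × 0.40 = 27.6.
- Difference 0.04. SE under the null = √(2 × 0.06 × 0.94 / 689) = 0.01280. SE under the alternative = √((0.08 × 0.92 + 0.04 × 0.96) / 689) = 0.01275.
- Chance of a two-sided 5% test showing a difference: Φ((0.04 − 1.96 × 0.01280) / 0.01275) = Φ(1.17) = 0.88.
- With true risks of 5% and 20% it is 0.59 and above 0.99.

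*Masked excess.* With complete recording, unpooled z:
- 5% against 8%: 34.5 and 55.1 events, z = 0.03 / √((0.05 × 0.95 + 0.08 × 0.92) / 689) = 2.26.
- 3% against 5%: 20.7 and 34.5 events, z = 1.90, short of 1.96 even with every event recorded.
- Under the SAE rule the control count would be near 0 and the intervention count only the part judged related, so neither contrast could be read from it.

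The rule can mislead in either direction. The figures show the mechanism, not the size to expect in this trial.

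**The case against.** The best reply is that between-arm safety does not depend on the SAE form. Deaths, emergency visits, hospital stays, falls and complications are recorded without a relatedness condition. Survival and hospitalisations are research questions in their own right, and secondary outcomes are to be compared between groups. Deaths are named beside SAEs in the DSMC's task, and accumulated trial data go to it. The article nowhere says that SAE counts will be compared by arm, and the layout of safety reports may be in the full protocol, which is not shown.

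Most of this stands, and it rules out several stronger readings:

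- *Safety cannot be compared between arms at all.* The unfiltered outcomes contradict this.
- *Controls can have no SAE.* Falls around study visits are open to them.
- *Non-serious events pass the same causal filter.* Their rule also admits events of concern, and the section says that they need not be causally related.
- *The investigator judging events is unblinded.* This is likely, since centres are told the allocation, but it is inferred. The safety section does not say whether that person knows the arm, and outcome assessors are blinded.

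The reply does not repair the SAE definition, which the article states in full rather than leaves to another document. Nor does any section make the unfiltered outcomes the basis of a safety comparison by arm.

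**Conclusion.** The point holds for SAE counts as defined: the two arms are counted by different rules, so a difference between them, or its absence, says little about safety. For non-serious events the problem is weaker. Entry rests on judgment at centres that know the allocation, and contact before surgery is very unequal.

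A reader might infer that the plan cannot detect harm or support any statement on safety. The article does not bear that out; what it shows is that SAE counts cannot carry the statement.

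The size of the distortion cannot be derived, because no event rates are given and the timing of surgery in controls is not stated. The conclusion rests on the wording of the definition and on controls receiving no study intervention, not on the assumed risks. The defect should be corrected, but it does not touch the primary analysis.

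**What to change.** 1. Use one entry rule in both arms from randomisation: every death, life-threatening event and unplanned admission. Record relatedness as a separate field.
2. Give the DSMC counts of these events by arm, split into randomisation to surgery and after surgery, filled from mortality, emergency-visit and hospital records.
3. At V6, ask both arms the same questions about the interval before surgery, because FIMA and the monthly contacts do not cover it.
4. Do not compare arms on SAE counts already gathered under the relatedness filter. Recruitment was due to end in June 2022, so for patients already past V6 the preoperative interval has to be filled from records.

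The cost is a change to the safety wording and the SAE form, more entries in a frail population, extraction from records, and a few added questions at V6. No new visit is needed. Existing data serve the time after surgery well but the preoperative interval only in part.

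### Listed SAE status for exercise-related events ends with the session, while falls at study visits are listed for 48 h, so delayed non-fatal admissions and procedures depend on investigator judgement

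*Protocol article*

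**What the plan says.** All of the reporting rules are in the protocol article, section Documentation and reporting of adverse and serious adverse events.

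- **General definition:** "Serious adverse events (SAEs) are defined as unexpected, fatal, or life-threatening events that are potentially related to the study intervention".
- **Deadline:** "An investigator must report the event in the eCRF within 72 h of the first notification".
- **Period and list:** "Serious adverse events will be reported up to 48 h after the last study visit, including the following". Two items come after this.
- **Item 1, exercise:** "Events occurring during prehabilitation sessions: falls, cardiac arrest, unscheduled hospitalization", then unscheduled intervention (a cardiac catheter is the example) and unscheduled surgery. No time after the session is given.
- **Item 2, study visits:** the window is "from the start of the visit up to 48 h after the visit): falls". Falls are the only event type in this item.
- **Other adverse events:** "Adverse events will be collected from the time of enrollment in the trial until 48 h after the final assessment", but the investigator decides which of them are recorded: "AEs will be documented as part of the study CRF if an event is considered to be of concern or related to the study". Events judged related to the intervention qualify as well. No reporting deadline is attached.

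On oversight, the section Management committee and data safety monitoring committee states: "As a primary responsibility, the DSMC will consider and assess treatment safety". It gives SAEs and deaths as examples and adds that accumulated trial data are reported to the DSMC.

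**The concern.** The two items treat time after contact in opposite ways. An assessment visit has a 48 h tail, for falls. The exercise session, which is the trial's exposure, has none for any of its five event types.

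The restriction also sits badly with the events it governs. A fall or a cardiac arrest can happen during a session. Hospitalization, an intervention or surgery is normally a consequence that follows it. Read literally, those three entries capture almost nothing. Read loosely, each centre and prehabilitation partner has to decide how long a session lasts for this purpose.

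What is at stake is how consistently and how quickly harms of the programme are reported. Participants are frail or pre-frail, aged 70 or older, and have two supervised sessions a day on five days a week. Delayed admissions and procedures are among the signals such a list should send to the DSMC.

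**Working it through.** **1. The rule applied to one case.** Take an unscheduled, non-fatal and non-life-threatening admission on the evening after a supervised session.

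| Route | Is the event captured? |
|---|---|
| Exercise item in the list | No, if read literally: it did not occur during the session |
| Study-visit item in the list | No: it covers falls only, and a session is not listed as a study visit |
| General SAE definition | Only if judged unexpected and potentially related; then a report within 72 h |
| AE documentation | If judged of concern or related; no deadline stated |
| Resource-use questionnaire (FIMA) | It records hospital stays as resource use; the Follow-up visits section schedules it at visits 9, 12 and 15, the first being 3 months after surgery |

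The general definition does not name hospitalization as a criterion. The same section also says that adverse events are to be expected in this population, which may lead an investigator to judge an admission as not unexpected. Automatic status is therefore lost, and reporting depends on judgement.

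For a cardiac arrest some hours after a session, the general definition has no session limit and the event is life-threatening. It is reportable if potentially related, so here the gap matters little.

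**2. Width of the listed window.** The plan states no figure to reproduce. Inputs are from the Prehabilitation section and Table 1 (30 supervised sessions of 30 min; six unsupervised sessions a week for 3 weeks) and Table 2 (V5 is 21 days after V4).

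- Programme length: 21 × 24 = 504 h.
- Supervised sessions: 30 × 0.5 = 15 h; 15/504 = 3.0%.
- Unsupervised sessions: 6 × 3 = 18. If all are done and last 30 min, 18 × 0.5 = 9 h; (15 + 9)/504 = 24/504 = 4.8%.

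**3. Width with the protocol's own 48 h added after each supervised session.** Session times are not given. Assume starts at 09:00 and 14:00, Monday to Friday. No gap between weekday sessions exceeds 48 h, so weekly cover runs from Monday 09:00 to Friday 14:30 plus 48 h, that is Sunday 14:30.

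- Per week: 6 × 24 + 5.5 = 149.5 h.
- Three weeks: 3 × 149.5 = 448.5 h; 448.5/504 = 89.0%.

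**4. Distance to surgery.** Table 2 puts V4 at 22 to 25 days before surgery and V5 at V4 + 21 days. V5 is therefore 22 − 21 = 1 to 25 − 21 = 4 days before surgery. A window running to V5 + 48 h reaches the operation whenever surgery falls within two days of V5. A 48 h window after a late session can do the same. Without a cut-off, surgical complications would be listed as prehabilitation events.

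**The case against.** The strongest reply is that the list is not the rule. It is introduced as an inclusion, and the general definition above it has no session limit, runs to 48 h after the last study visit and carries the 72 h deadline. Its three terms are alternatives, so an unexpected and potentially related admission is already an SAE whenever it occurs. An unscheduled catheterisation soon after exercise is a natural candidate. An admission recognised as exercise-related would at least be documented as an AE. The exercise item may also be meant to cover events that arise in a session and lead to admission, and the full protocol, which is not shown, may say so.

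Most of this stands, and it rules out several stronger readings:

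- A reader might infer that delayed events escape mandatory reporting. They do not as a class; they lose automatic status.
- A reader might infer that most exercise-related admissions would never reach the DSMC, or that the safety conclusion will be too favourable. The article gives no event rates or timings to support either, and accumulated trial data also go to the DSMC.
- A reader might take the 95–97% of programme time outside sessions as the share of events missed. It is clock time only. Exercise-related events are not spread evenly over it, and many outside sessions would meet the general definition.

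What the reply does not remove is the wording. If the list is meant to relieve sites of judging these five event types, it fails for three of them. If later consequences were intended, the text does not say so, although the next item shows how to say it.

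**Conclusion.** The point holds as a defect in how the listed window is fixed. Automatic SAE status for five event types is confined to session time, while falls at study visits are listed for 48 h. Non-fatal, non-life-threatening hospitalizations, interventions and operations that follow a session by hours become mandatory 72 h reports only on a judgement of unexpectedness and potential relatedness; otherwise AE documentation is at the investigator's discretion.

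In time terms the listed window is 3.0% of the programme (4.8% with unsupervised sessions of 30 min), against about 89% with 48 h after supervised sessions. The 89% rests on the assumed weekday timetable. The number of events affected cannot be estimated from the article. The finding rests on the article's wording alone. No sample size, power or efficacy result is affected. It is a cheap improvement to safety reporting, not evidence that harms will go unreported.

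**What to change.** Reword the exercise item so that it covers events from the start of a prehabilitation session until 48 h after it, or until the start of the elective surgery, whichever is earlier. Apply this to all five listed event types and state that unsupervised sessions count. Repeat the rule in the eCRF guidance.

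The cut-off at surgery is needed because V5 lies only 1 to 4 days before the operation. A simpler window from V4 to V5 + 48 h would serve only with the same cut-off.

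The cost is one sentence in the protocol, a line of eCRF guidance and somewhat more SAE reports from prehabilitation sites, some of them unrelated to exercise. The investigator's relatedness assessment would still be recorded, but it would no longer decide whether these events are reported.
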